## Abstract

**Background:**

SARS-CoV-2 has been responsible for a worldwide public health crisis and a pandemic that began in February 2020, with approximately 679 million cases and over 6.7 million deaths to date. Despite the existence of approved COVID-19 vaccines, these vaccines are either based on mRNA technology or viral vectors. Imam Abdulrahman Bin Faisal University (IAU) has developed a thermally stable plasmid DNA (pDNA)-based vaccine candidate using a platform approach that enables the rapid development of vaccines against emerging viral diseases. The pDNA vaccine developed by IAU encodes the full-length, optimized version of the SARS-CoV-2 Spike protein. Key advantages of this pDNA vaccine are that it is cost-effective, thermally stable, and can be used to administer multiple immunizations without incurring anti-vector responses, making it a promising candidate as a vaccine booster dose.

**Methods:**

This study aims to investigate the safety, tolerability, and immunogenicity of this prophylactic pDNA vaccine as a booster vaccine to protect against COVID-19 when administered as an intramuscular injection in a single ascending dose design. In total, 42 eligible healthy subjects will be enrolled in the study. The subjects will be randomized to receive either the investigational vaccine or placebo (Saline) at a 3:1 allocation ratio. Participants will have received two doses of a SARS-CoV-2 mRNA vaccine at least 4 months prior to enrollment. Subjects will be enrolled in a dose-escalating study and assigned to one of the three cohorts (Cohort 1: low-dose; Cohort 2: mid-dose; Cohort 3: high-dose). Primary endpoints will include local reactions and systemic reactions for up to 7 days following vaccination, adverse events from vaccination to 1 month, and serious adverse events from vaccination to 6 months. Secondary endpoints will include the evaluation of binding antibody (bAB) and neutralizing antibody (nAB) responses at vaccination day (Visits 1) and 30 days after vaccination (Visit 4), the ratio of bAB to nAB titers at Visits 1 and 4, and cellular immune responses (CD3, CD4, CD8, CD45RA, CCR7, IFN-γ, IL-2, IL-4, IL-13, and TNF) at Visits 1 and 4.

**Discussion:**

The study will be critical to determine the safety and immunogenicity of the pDNA vaccine in participants who have previously received a COVID-19 mRNA vaccine. This study will also aim to determine the safest maximum tolerated dose in participants receiving the pDNA vaccine.

**Trial registration:**

ClinicalTrials.gov SCTR No 23010802.

## Introduction

### Background and rationale {6a}

The rapid development of vaccines against Severe Acute Respiratory Syndrome Coronavirus 2 (SARS-CoV-2) was a significant scientific achievement in modern history, with multiple vaccines receiving authorization and approval for emergency use (1–4). Despite these efforts, the burden of COVID-19 remains substantial, particularly in low to middle income countries (LMIC), where lower vaccination rate contributes to the contious emergence of variants of concern (VOC) (5). Besides, vaccine side effects have been documented, including the risk of myocarditis and pericarditis in adolescents and young adults aged 18–24 (4, 6, 7). Furthermore, individuals with a history of allergic reactions may have an elevated risk of an allergic reaction following mRNA vaccination, likely due to the PEG component included in the lipid nanoparticles of mRNA vaccines components (8). Given that the current mRNA vaccines strictly require ultra-cold storage to remain effective, there is an ongoing need for developing thermally stable vaccines that can be easily distributed and stored, especially in countries lacking robust ultra clod chain infrastructure (9, 10).

For these reasons, there is a clear need to explore alternative vaccine platforms that can overcome the limitations associated with currently approved COVID-19 vaccines. Plasmid DNA (pDNA) vaccine technology has an inherit ability to produce a targe antigen which then trigger immune responses (11–13).

Recent years have seen rapid improvements in the development of pDNA vaccine platforms, with various pDNA vaccine candidates having progressed to Phase II/III clinical trials (14–19). There are several advantages to pDNA vaccines. For one, when compared with mRNA vaccine platforms, pDNA is more stable, such that ultra cold-chain shipment and storage are not needed (11, 12). In addition, the potential for anti-vector immunity generated after immunization with a viral vector vaccine is not a concern for the pDNA vaccine platform. Moreover, pDNA vaccine platform is generic and adaptable to high scale manufacturing (11, 12). While concerns regarding the theoretical potential for vector DNA integration have been raised, previous preclinical and clinical studies on the tested DNA vaccine candidates following intramuscular immunization revealed no evidence of such integration into the genomes of host cells (20, 21). However, one notable disadvantage of the pDNA vaccine platform is that it tends to be associated with relatively low immunogenicity in humans. This finding has spurred a range of approaches to enhancing immunogenicity, such as gene insert optimization (12).

Imam Abdulrahman Bin Faisal University (IAU) has developed an investigational prophylactic COVID-19 pDNA vaccine using a codon-optimized version of the SARS-CoV-2 gene encoding the spike (S) protein (S.opt.FL). This vaccine ([name]-001), consists of a pDNA carrying an optimized, full lenghth Spike (S.opt.FL) gene insert (22) from the wild-type SARS-CoV-2. The plasmid backbone included in the study is (pVAX-1), an FDA-approved plasmid for application in clinical trials. Moreover, the vaccine is administered intramuscularly (IM) without the need of physical delivery approaches, such as electroporation or gene gun. The preclinical study conducted at IAU has demonstrated that S.opt.FL is immunogenic in mice (22). The study found that S.opt.FL elicited high binding antibody (bAB) and neutralizing antibody (nAB) as well as a strong interferon (IFN)-γ response consistent with cellular immunity (22). In addition, a subsequent protective efficacy study in Syrina Golden hemesters indicated that this S.opt.FL pDNA vaccine candidate is safe and effective in preventing SARS-CoV-2 infection (23).

Previous work on pDNA vaccines encoding the S gene of SARS-CoV, MERS-CoV, and SARS-CoV-2 has demonstrated that pDNA-based vaccines are safe and well-tolerated (24–26). Due to increasing vaccination coverage worldwide, the WHO and International Coalition of Medicine and Regulatory Authority (ICMRA) have issued guidance regarding the design of clinical trials for next-generation COVID-19 vaccines in the context of the availability of authorized COVID-19 vaccines. These recommendations include the testing of next-generation vaccines as booster doses in vaccinated individuals (27).

The purpose of this clinical trial is to evaluate the safety and immunogenicity of a single dose of an investigational pDNA vaccine encoding the S.opt.FL gene of inserted into the pVAX1 plasmid relative to placebo control. In this Phase 1 study, the pDNA vaccine candidate will be administered intramuscularly (IM) as a booster dose to immunize healthy adults previously vaccinated with mRNA vaccine (18–55 years). The utilized S.opt.FL pDNA vaccine will be evaluated through a single ascending dose study design with three different cohorts administered low, intermediate, and high doses of pDNA.

#### Dose rationale

The starting dose selected for this study was based on the starting dose of 1 mg/ml used in the pivotal non-clinical toxicity study. The repeated toxicity study was designed in line with the immunization schedule in this study, reflected by the number of doses and immunization intervals. Details are described in the Investigator's Brochure (IB). The tested S.opt.FL COVID-19 pDNA vaccine candidate ([name]-001) demonstrated high immunogenicity and a good safety profile in multiple tested animals (Mice, Syrian Golden Hamsters, New Zealand White Rabbits). Further, the repeated dose toxicology study demonstrated the safety and tolerability of the clinical-grade preparation of the investigational vaccine. No vaccine-related clinical signs or mortality were observed.

#### Risk-benefit assessment

##### Risk and mitigation

The potential risks associated with study participation will be minimized by implementing adequate inclusion/exclusion criteria. Risks associated with any vaccination include local injection site reactions (i.e., pain, redness, and swelling at the injection site) and systemic events (including fever, fatigue, headache, chills, vomiting, diarrhea, muscle and joint pain) which will be carefully monitored through safety evaluation procedures. Potential risks that may be associated with the COVID-19 pDNA vaccine product are summarized in Table 1.

**Table 1 T1:** Risk-benefit assessment.

Potential risk	Data/Rationale of the risk	Mitigation strategy
Potential risk of local reaction (pain, redness, and swelling at the injection site) and systemic events (fever, fatigue, headache, chills, vomiting, diarrhea, muscle and joint pain)	These potential adverse reactions are also associated with other vaccines and are described in the protocol through the implementation of FDA guidance for toxicity grading	The study protocol design includes the implementation of controlled vaccination per cohort that is closely monitored to limit the rate of enrollment to ensure participant safety. The first two participants for each randomized cohort will be observed for 4 h to assess any immediate AEs, with each subject being monitored for 60 min before proceeding to the next subject. The next four participants will be dosed only after 48 h and after safety review of the first four participants, and each will be monitored for 2 h. The rest of the subjects (*n* = 10) will be enrolled after 24 h and will be monitored for 2 h. Dose escalation for the subjects in the next cohort will not occur until 12–14 days and after DMC reviews the accumulated safety data. Stopping rules are also applied in the protocol. The study employs the use of a diary to monitor local reactions and systemic reactions. Safety measures are instituted to closely monitor participants' safety during this clinical study and to assess risks associated with administration of the investigational product.
Potential unknown AEs and laboratory abnormalities associated with novel vaccine	This is a first–in–human Phase I study with clinical data available	The study protocol design includes the implementation of controlled vaccination per cohort that is closely monitored to limit the rate of enrollment to ensure participant safety. The first two participants for each randomized cohort will be observed for 4 h to assess any immediate AEs, with each subject being monitored for 60 min before proceeding to the next subject. The next four participants will be dosed only after 48 h and after safety review of the first four participants, and each will be monitored for 2 h. The rest of the subjects (*n* = 10) will be enrolled after 24 h and will be monitored for 2 h. Dose escalation for the subjects in the next cohort will not occur until 12–14 days and after DMC reviews the accumulated safety data. Stopping rules are also applied in the protocol. The study employs the use of a diary to monitor local reactions and systemic reactions. Safety measures are instituted to closely monitor participants' safety during this clinical study and to assess risks associated with administration of the investigational product.
Theoretical risk of possible DNA integration and prolonged expression	The risk that a pDNA vaccine may integrate into the recipient's DNA has been only theoretical to date	The plasmid backbone of IAU COVID-19 vaccine is an FDA-approved plasmid (pVAX1) that has been tested in numerous clinical trials with an excellent safety profile. The pVAX1 plasmid does not encode a mammalian expression system or molecular adjuvants.
Low immunogenicity	Low pDNA vaccine–associated immunogenicity in humans	Codon optimizations of the S gene insert was implemented to increase expression.

##### Benefits

There are no known direct benefits to the participants enrolled in this study. The IAU COVID-19 pDNA vaccine is expected to elicit an immune response against the original SARS-CoV-2 strain. Information gained from this trial will help with the following:

To support the ongoing development of an improved COVID-19 vaccine that can overcome the limitations of currently approved vaccines.To support the clinical development and application of pDNA vaccine platforms.

##### Overall risk-benefit assessment

The IAU COVID-19 vaccine is in the early clinical stages of testing, as it has not undergone prior clinical testing. However, considering the minimal potential risks associated with the study and the medical measures that will be implemented to minimize the risk to healthy subjects, the overall risks are justified by the potential benefit linked to the development of an improved COVID-19 vaccine.

### Objectives {7}

The objective of this study is to evaluate the safety, tolerability, and immunogenicity of the COVID-19 pDNA vaccine product in healthy individuals through a dose escalation study with a single ascending dose design. The trial objectives, assessment, and endpoints are summarized in Table 2.

**Table 2 T2:** Trial objectives, estimands, and endpoints of the phase-I clinical trial.

Objectives	Estimands	Endpoints
Primary	Primary	Primary
To assess the safety and tolerability of the investigational COVID-19 pDNA vaccine compared to placebo	• Local reactions for up to 7 days following Vaccination (Visit 1) • Systemic events for up to 7 days following Vaccination (Visit 1) • AEs from vaccination (Visit 1) to (Visit 4) • SAEs from vaccination (Visit 1) to (Visit 5)	• Assessment of administration site reactions (local reactions) • Assessment of systemic AEs • Clinical assessment of participants health status • Clinical laboratory investigations • Monitoring of participants' COVID-19 infection status • Recording of solicited and unsolicited AEs and SAEs
Secondary	Secondary	Secondary
To assess binding and neutralizing antibody responses to the investigational COVID-19 pDNA vaccine compared to placebo	• bAB responses at (Visit 1) and (Visit 4) • nAB responses to the investigational pDNA vaccine at (Visit 1) and (Visit 4) • Ratio of bAB and nAB titers at (Visit 1) and (Visit 4). • Fold rise (GMFR) in serum anti-S, anti-S1, and anti-RBD binding antibody titers at (Visit 1) and (Visit 4).	• bAb responses against the S, S1, and RBD proteins of SARS-CoV-2 • Fold rise in bAB responses against the S, S1, and RBD proteins of SARS-CoV-2 • nAb responses against the S protein of SARS-CoV-2 • Fold rise in anti-S nAB titers for SARS-CoV-2 • bAB and nAB ratios for the S protein of SARS-CoV-2
To assess T cell and intracellular cytokine responses to the investigational COVID-19 pDNA vaccine compared to placebo	• Cellular immune response at (Visit 1) and (Visit 4)	Cellular immune responses (CD3, CD4, CD8, CD45RA, CCR IFN-γ, IL-2, IL-4, IL-13, and TNF)
Exploratory Objective	Exploratory	Exploratory
Humoral Response to SARS-CoV-2 Variants of Concern in response to the investigational COVID-19 pDNA vaccine compared to placebo	• bAB responses against SARS-CoV-2 VoC • nAB responses against SARS-CoV-2 VoC • bAB and nAB ratio for SARS-CoV-2 VoC	• bAB responses against SARS-CoV-2 VoC): (alpha, beta, Gamma, Delta, and Omicron) • nAB responses against SARS-CoV-2 VoC): (alpha, beta, Gamma, Delta, and Omicron) • bAB and nAB ratio for SARS-CoV-2 VoC): (alpha, beta, Gamma, Delta, and Omicron)

AEs, adverse events; SAE, severe adverse events; bAB, binding antibody; nAB, neutralizing antibody.

#### Primary objective (safety and tolerability)

To assess the safety and tolerability of the investigational pDNA COVID-19 vaccine in healthy adults when administered as a single dose vs. placebo.

##### Assessments

Local reactions (i.e., reactogenicity) for up to 7 days following vaccination.Systemic events for up to 7 days following vaccination.Adverse events (AEs) for up to 1 month following vaccination.Serious AEs (SAEs) for up to 6 months following vaccination.

#### Secondary objectives (immunogenicity)

To assess S-specific bAB and nAB responses as indicators of humoral immune response after vaccination compared to placebo.To assess T cell and intracellular cytokine responses as indicators of cell-mediated immune response after vaccination compared to placebo.

##### Assessments: humoral response to wild-type SARS-CoV-2

Evaluation of S-specific bAB responses to the investigational pDNA vaccine vs. placebo at Visit 1 (baseline) and Visit 4 (30 days after Visit 1).Evaluation of S-specific nAB responses to the investigational pDNA vaccine vs. placebo at Visit 1 and Visit 4.Comparison of the ratio of bAB to nAB titers directed against the investigational pDNA vaccine vs. placebo at Visit 1 and Visit 4.Determination of the geometric mean fold rise (GMFR) in the serum S-specific, anti-S1-specific, and anti-RBD bAB titers directed against the investigational pDNA vaccine vs. placebo at Visit 1 and Visit 4.

##### Assessments: cell-mediated Responses to wild-type SARS-CoV-2

Evaluation of cellular immune response by measuring CD3, CD4, CD8, CD45RA, CCR7, IFN-γ, IL-2, IL-4, IL-13, and TNF after investigational pDNA vaccine vs. placebo.

#### Exploratory objective (immunogenicity)

To further explore the immunogenicity of the investigational pDNA vaccine against the SARS-CoV-2 variants of concern in vaccinated subjects vs. placebo.

### Trial Design {8}

This investigational vaccine study is a Phase 1, randomized, dose-finding, single-center study, enrolling healthy adults. In total, 42 healthy individuals will be enrolled in the study. The eligible individuals will be randomized to receive either the investigational vaccine or placebo (Saline). Subjects will be enrolled at a 1:1:1 ratio in a dose-escalating manner to one of three cohorts (Cohort 1: low dose level, “1 mg”; Cohort 2: mid-dose level, “2 mg”; Cohort 3: high-dose level, “4 mg”). All subjects will receive a single dose of the vaccine or placebo IM.

The study duration for an individual subject is approximately 7 months. Interim analysis for safety will be performed on the data that are collected from all study subjects at Visit 1, Visit 2 (1 day after Visit 1), Visit 3 (7 days after Visit 1), and Visit 4, while interim analysis for immunogenicity will be performed on the data that are collected from all study subjects at Visit 1 and Visit 4. Table 3 illustrates the schedule of activities (SOA) and timing of study visits and assessments.

**Table 3 T3:** Schedule of study visits and assessments—Visit 1 to Visit 5.

Visit number	Screening	1	2	3	4	5	Unplanned	Unplanned
Visit description	Screening	Vax 1	Next-Day Follow-up Visit (Vax 1)	1-Week Follow-up Visit (Vax 1)	1-Month Follow-up Visit	6-Month Follow-up Visit	Potential COVID-19 Illness Visit	Potential COVID-19 Convalescent Visit
Visit window (Days)	0 to 28 Days Before Visit 1	Day 1	1 to 3 Days After Visit 1	6 to 8 Days After Visit 1	28 to 35 Days After Visit 1	154 to 168 Days After Visit 1	Optimally Within 3 Days After Potential COVID-19 Illness Onset	28 to 35 Days After Potential COVID-19 Illness Visit
Physical examination (height, weight, BMI, vital signs, general appearance, examination of skin, auscultation of the heart, auscultation of the lungs, palpation of the abdomen, examination of extremities)	X	X	X	X	X	X		
ECG	X			X				
Collect blood sample for hematology and chemistry^a^	~13.5 ml	~13.5ml	~13.5 ml	~13.5 ml	~13.5 ml	~13.5 ml		
Collect screening blood sample for HIV, HBsAg, HBc Ab, and HCV Ab tests	X included in chemistry sample							
Perform alcohol test	X							
Perform drug panel test	X							
Perform serum pregnancy test (if appropriate)	X							
Perform urine pregnancy test (if appropriate)		X				X		
Urinalysis^a^	X	X				X		
Obtain nasal swab (mid-turbinate) for COVID-19	X	X^b^					X	
Collect non-study vaccine information	X	X	X	X	X	X		
Confirm eligibility	X	X						
Collect prohibited medication use	X	X	X	X	X	X	X	X
Review hematology and chemistry results^c^	X	X	X	X	X	X		
Review temporary delay criteria		X						
Confirm use of contraceptives (if applicable)	X	X	X	X	X			
Obtain randomization number and study intervention allocation		X						
Collect blood sample for immunogenicity assessment^a^		~20 ml			~20 ml	~20 ml (optional 50 mL^d)^		
Administer study intervention^c^		X						
Assess acute reactions after study intervention administration^c^		X						
Explain participant communication methods (including for diary completion)		X						
Provide thermometer measuring device		X						
Provide diary to subjects		X						
Review reactogenicity diary data			X	X	X	X		
Review ongoing reactogenicity diary symptoms and obtain stop dates			X	X				
Collect diary to assess participant				X				
Collect AEs and SAEs as appropriate	X	X	X	X	X	X	X	X
Collection of COVID-19-related clinical and laboratory information							X	X

HBc Ab, hepatitis B core antibody; HBsAg, hepatitis B surface antigen; HCV Ab, hepatitis C virus antibody; HIV, human immunodeficiency virus; min, minutes; NAAT, nucleic acid amplification test; vax, vaccination.

^a^Availability of results will not delay further study activities.

^b^Two swabs will be taken at 1–2 days prior to Visit 1. One will be tested (at the site, if possible, otherwise at the central laboratory) within 48 h, and vaccination will only proceed if it is NAAT-negative for SARS-CoV-2 genomes. The second will be sent to the central laboratory for potential later testing.

^c^The first two participants vaccinated in each cohort will be observed at the site for at least 4 h after study intervention administration, with each subject to be monitored for 60 min before proceeding to the next subject. The next four participants in each cohort may be vaccinated at least 48 h after the first two participants have completed their Visit 2 safety data review and completed 48 h post-vaccination, and they will also be observed for at least 4 h after study intervention administration at the study site. Vaccination of the rest of the subjects in each cohort will commence no sooner than 24 h after the sixth participant has received their vaccination. Post-immunization local and systemic AEs and vital sign measurements will be performed by site staff at hourly intervals. After 4 h post-vaccine administration through 7 days after vaccination, solicited local and systemic AEs and body temperature measurements will be reported daily by the study participant.

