## Assignment of intervention: allocation

### Randomization {16}

When an individual is determined to be eligible to participate in the study, the subject will be enrolled in a computerized randomization system that assigns a designated subject ID to allocate them to receive either the COVID-19 pDNA vaccine or placebo using Interactive Response Technology (IRT). Each cohort will contain 14 subjects. At Visit 1, the first two subjects of each cohort will be randomized according to a separate randomization list. One subject will be randomized to placebo, and one subject will be randomized to the study treatment to ensure that at least one subject will receive the study vaccine. They will be monitored for 4 h, with each subject to be monitored for 60 min before proceeding to the next subject. The next four participants in each cohort will be vaccinated at least 48 h after the first 2 participants complete their visit 2 safety data review. They will also be observed for at least 4 h at the study site. Vaccination of the rest of the subjects in each cohort will commence no sooner than 24 h after the sixth participant has undergone vaccination. All subjects in the dosing visit (Visit 1) will be observed for 4 h.

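### The within-cohort dosing steps are described in conflicting ways, and the operational text opens the last eight doses 24 h after the sixth injection without requiring a review of subjects 3–6

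*Protocol article*

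**What the plan says.** All places are in the Protocol article.

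- **Last step.** Table 3 footnote c: vaccination of the rest of each cohort "will commence no sooner than 24 h after the sixth participant has received their vaccination". Randomization {16} and Plan for assessment and collection of outcomes {18a} repeat this 24 h rule. None of the three mentions a review of subjects 3–6.
- **First gate.** Footnote c and {18a} allow the next four to be dosed at least 48 h after the "first two participants have completed their Visit 2 safety data review and completed 48 h post-vaccination". Section {16} has them "vaccinated at least 48 h after the first 2 participants complete their visit 2 safety data review". Table 1 asks for 48 h plus a safety review of four participants.
- **First pair.** Section {16}: "One subject will be randomized to placebo, and one subject will be randomized to the study treatment". Section {18a} describes both as receiving the vaccine.
- **Observation.** Section {16}: "All subjects in the dosing visit (Visit 1) will be observed for 4 h". Table 1 gives 4 h to the first two and 2 h to everyone after them.
- **Size of the last step.** Table 1 gives n = 10. Section {18a} inserts another group of four after the sixth subject and before the remainder. Section {16} fixes the cohort at 14.
- **When data arrive.** Visit 2 is the next-day visit, with a window of "1 to 3 Days After Visit 1" in Table 3. Footnote a, on the blood sampling row, adds: "Availability of results will not delay further study activities".
- **Other cover.** After 4 h and through day 7, "solicited local and systemic AEs and body temperature measurements will be reported daily by the study participant" (footnote c). AEs go to the sponsor and the DMC ({22}). Stopping rules apply throughout.

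**The concern.** This is a first-in-human product given as one injection that cannot be withdrawn. Dosing in steps protects participants only if what is learned at one step can change the next. The article attaches a safety data review to the step that exposes four people, but only a waiting time to the step that exposes eight.

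The stopping rules respond to events that reach a threshold. One related Grade 4 event or SAE stops dosing. The Grade 3 rule needs two or more participants. A lone related, non-serious Grade 3 event among the first six subjects of cohort 1 therefore triggers no stop, and no planned look is required before the other eight are injected. In cohorts 2 and 3 an earlier event may count towards the two.

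Separately, site staff have four accounts of the same procedure. They differ on who is in each step, how long to wait, what must be reviewed and how long to observe. Table 1 is the risk-mitigation table, so the safeguard presented there is not the one that the operational text describes.

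**Working it through.** **1. Head counts.**

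| Source | Steps | Total |
|---|---|---|
| Footnote c, {16} | 2 + 4 + 8 | 14 |
| Table 1 | 2 + 4 + 10 | 16 |
| {18a}, extra group read as a further tier | 2 + 4 + 4 + 4 | 14 |

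Table 1's n = 10 would fit 2 + 2 + 10 = 14. That would also explain its review of four, but the same cell says that the second group is four. The last step under footnote c and {16} is 14 − 6 = 8, and 8/14 = 57%.

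**2. First gate.** Table 1 gives 48 h after dosing. Under {16} it is 48 h after the Visit 2 review. With Visit 2 at 1 day, that is at least 24 + 48 = 72 h after dosing. Footnote c and {18a} can be read either way.

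**3. Timing of the last step.** It may open 24 h after subject 6 is injected. Visit 2 for subjects 3–6 is nominally at 1 day, so on schedule it falls about when the step opens. At the edge of the window (day 3) it falls up to 2 days later. Nothing in footnote c, {16} or {18a} holds the step until those visits are done.

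**4. Vaccinees reviewed before the last step.** Inputs are 14 per cohort, 3:1 allocation, and a first pair of one vaccinee and one placebo recipient.

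- 14 × 0.75 = 10.5, so a cohort has 10 or 11 vaccinees and 4 or 3 placebo recipients.
- After the first pair, subjects 3–14 hold 9 vaccinees and 3 placebo recipients, or 10 and 2.
- Assume the remaining placebos are spread at random over subjects 3–14. The chance of k vaccinees among subjects 3–6 is C(V, k) × C(P, 4 − k) / C(12, 4), with C(12, 4) = 495.

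| k | V = 9, P = 3 | V = 10, P = 2 |
|---|---|---|
| 1 | 9/495 = 0.02 | 0 |
| 2 | 108/495 = 0.22 | 45/495 = 0.09 |
| 3 | 252/495 = 0.51 | 240/495 = 0.48 |
| 4 | 126/495 = 0.25 | 210/495 = 0.42 |

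Reviewed vaccinees as written: 1. With a review of subjects 3–6 added: 1 + k = 2 to 5, with 4 most likely (about 50%). The last step then holds 5 to 8 vaccinees, and 10 − 4 = 6 or 11 − 4 = 7 in the most likely case.

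**The case against.** **A minimum wait does not order dosing to proceed, and an article condenses.** The full protocol or DMC charter may set a go/no-go decision between steps. This stands as a caveat. It does not remove the point, because the article writes out a review at the first gate and then states the second as elapsed time in three places. The contradictions are also in the text as published.

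**Table 1 does ask for a review beyond the first pair.** A reader might infer that no text anywhere requires more than the first pair to be reviewed. Table 1 does not support that. But its review of four is placed when two have been dosed, cannot be carried out in that order, and is absent from footnote c, {16} and {18a}.

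**Subjects 3–6 are not unwatched.** A reader might infer that they are, or that the DMC sees nothing at a dose until the cohort is complete. The documents do not support either reading. There is 4 h observation, daily reporting, AE notification to the sponsor and DMC ({22}), DMC review of data from periodic visits ({5d}) and investigator and sponsor monitoring (Stopping rules). Only the escalation decision is tied to the interval between cohorts. What remains is that {22} sets no deadline for non-serious AEs, so notice before the last step is not assured.

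**Visit 2 is normally next-day.** That is so, and day 3 is the edge of the window. Still, no rule makes the last step wait for it.

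**Two further inferences go too far.** Footnote c might be read as two successive 48 h waits (96 h), but a review plus a single 48 h wait is at least as natural. It is best called ambiguous. A reader might also want the extra vaccinees turned into a chance of catching a reaction. The article gives no event rates, so any such figure would rest wholly on assumed risks.

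**Conclusion.** The point holds as a should-fix. The staging rules conflict on counts (14 against 16), observation (4 h against 2 h), first-pair make-up, an extra group of four and the length of the first wait. In the operational sections, 8 of 14 subjects per cohort may be dosed when the only review clearly required at that dose covers one vaccinee.

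It is not more serious than that, because event-triggered cover exists and single related Grade 4 events and SAEs stop dosing. The gap is a planned look at events that appear late or stay below the thresholds. The head counts follow from the text alone. The most likely figure of 4 reviewed vaccinees assumes random placement of the remaining placebos. The conclusion on the review also assumes that no document outside the article already requires it.

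**What to change.** Use one scheme in footnote c, {16}, {18a} and Table 1:

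- **Steps:** 2 (one vaccine, one placebo) + 4 + 8 = 14, with 4 h observation for all.
- **First gate:** Visit 2 review of the first pair complete and at least 48 h post-vaccination.
- **Last step:** opens only after subjects 3–6 have each reached at least 48 h and their Visit 2 and diary data have been reviewed. The reviewer may proceed, wait, or refer to the DMC, for example for a lone related non-serious Grade 3 event.
- **Also state** who carries out both reviews, which the article does not name, and whether Visit 2 laboratory results are needed. The results-review row carries footnote c, while footnote a on the sampling row says that results do not hold up activities.

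The cost is amendment wording and a short delay, using existing visits and diaries. Moving from 24 h to 48 h adds 1 day. A Visit 2 on day 3 makes it 2 days, and up to 1 day for the review (assumed) makes it 3. That is 1–3 days per cohort, or 3–9 days over three cohorts. The two between-cohort waits of 12–14 days already take 24–28 of the 28–42 days planned for recruitment ({15}), so the added days may press on that period. How much depends on whether each wait runs from a cohort's first or last dose, which {5d} does not say.
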